#### Secondary outcome(s)

Difference in proportions of infants with developmental delay between the DHA and placebo group at 12 months. Developmental delay will be defined as a DASII score ≤ 70.Mean difference in infant size (weight, length and head circumference) and APGAR score at birth.Mean change in infant size (weight, length and head circumference) at birth, 1 month, 6 months and 12 months between the DHA and placebo group.Mean difference in number of still births, preterm and low birth weight babies between DHA and placebo groups.Difference in infant morbidity patterns (types of illness, frequency and duration of specific conditions) between DHA and placebo group.

#### Tertiary outcomes

Difference in DHA values (as measured by fatty acids in maternal blood) from baseline to delivery and 6 months post-partum in the two treatment groups.Difference in DHA values (as measured by fatty acids in cord blood and breast milk) in the two treatment groups.

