**Methods:**

DHANI is a double-blinded, parallel group, randomized, placebo controlled trial supplementing 957 pregnant women aged 18–35 years from ≤20 weeks gestation through 6 months postpartum with 400 mg/d algal-derived DHA or placebo. Data on the participant’s socio-demographic profile, anthropometric measurements and dietary intake are being recorded at baseline. The mother-infant dyads are followed through age 12 months. The primary outcome variable is infant motor and mental development quotient at 12 months of age evaluated by Development Assessment Scale in Indian Infants (DASII). Secondary outcomes are gestational age, APGAR scores, and infant anthropometry. Biochemical indices (blood and breast-milk) from mother-child dyads are being collected to estimate changes in DHA levels in response to supplementation.

All analyses will follow the intent-to-treat principle. Two-sample t test will be used to test unadjusted difference in mean DASII score between placebo and DHA group. Adjusted analyses will be performed using multiple linear regression.

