### Effect size, power and sample size

The primary outcome variables are infant motor and mental development quotient at 12 months of age. The smallest effect sizes of interest were 0.25 S.D. for motor and mental development at 12 months of age [42]. Using a two-tailed test and a significance level of α = 0.05, a final sample of 338 infants per group (676 mother-child dyads) was required at the end of the study (12 months postpartum) to provide 90% power. A total of 957 mothers have been recruited in the present study, allowing for potential attrition due to serious adverse events, withdrawal, and migration out of the study area. Breast-milk samples are being collected within 3–4 days after delivery and at 1 month and 6 months postpartum from a 30% convenience sub-sample - 150 mother-infant pairs per group, which will have 95% power to detect effect sizes of 0.5 S.D. in DHA levels.

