Secondary outcomes:Birth outcomes – Data are collected by a research assistant from hospital records within 24 h after delivery. In case of night deliveries, records from hospital staff are obtained the next morning. All hospital staff were apprised of the variables being collected, procedures and data collection methods before the start of the trial. A periodic (every 6 months) refresher training has also been provided to the staff. The data include whether the birth was a live birth, sex of baby, type of delivery, and anthropometric measurements. Birth weight is measured to the nearest 10 g by using a digital pediatric scale. Low birth weight is defined as recorded birth weight less than 2500 g. Birth length and head circumference are measured by trained hospital staff to the nearest 1 mm using a portable anthropometer with a fixed headpiece and a flexible tape, respectively, according to standard procedures. Gestational age at birth in days is determined based on the dating ultrasound. Preterm delivery is defined as delivery after 20 weeks and before 37 weeks of completed gestation. Foetal losses during pregnancy – including miscarriages/abortions and still-births are recorded by study personnel on site or details are brought by field workers (in case mother went to any other hospital). Stillbirths are defined as fetuses delivered at 20 weeks of gestation or later with no signs of life and recorded as occurring before or during the onset of labor; neonatal deaths are defined as deaths among live-born infants occurring within 28 days after delivery.Infant weight, length and head circumference at 6 and 12 months are measured during their scheduled PKH visits. Questions about infant’s health are asked by the field-staff during home-visits (postpartum). Copies of the health-reports from the child’s paediatrician (whether at PKH or elsewhere) are collected. After the screening procedure, at the time of recruitment, data for contact information, maternal obstetric medical history, demographic details and socio-economic status also have been collected by the trained research assistant using pre-tested questionnaires. Anthropometric measurements of both mother and father have been recorded. Dietary intakes of fatty acids were evaluated using a previously validated food-frequency questionnaire adapted for use in pregnant women (recall period- past 3 months) also have been recorded.Fatty acid profile: Fatty acid composition of RBC membrane phospholipids are appropriate biomarkers of fatty acid status and reflects dietary intakes. Linoleic acid (18:2n-6); Alpha-linolenic acid (18:3n-3); Arachidonic acid (20:4n-6); Eicosapentanoic Acid (20:5n-3); DHA (22:6n-3) will be measured for this study. Lipids will be extracted form the RBC membrane, phospholipid fraction will be separated by thin layer chromatography (TLC), esterified by procedure described by Lepage and Roy [49] and subjected to gas chromatography (GC) for separation and identification. Non fasting maternal blood samples (5 ml) were obtained by veni-puncture at recruitment, delivery and 6 months postpartum. Neonatal blood samples were obtained from the umbilical cord vein immediately after delivery using the syringe method [50]. A 2 ml venous blood sample was obtained 12 months of age from infants. All samples were collected into tubes containing disodium ethylene diamine tetraacetic acid (EDTA). Plasma and RBCs were separated by cold centrifugation at 800 g for 10 min. Plasma was aliquoted and stored at − 80 °C for later analysis.Breast-milk polyunsaturated fatty acids (PUFAs): Breast-milk samples (1 day, 1 month and 6 months postpartum) are taken from 30% random sub-sample. The milk-samples are from a morning feed but not the first one, between 8 and 12 o’clock at PKH. Infants are allowed to suckle the nipple for a few minutes, and then a breast-milk sample (10 ml) is expressed (manual, by mothers themselves) and the feeding continued [51]. The samples are refrigerated immediately (to prevent bacterial growth) and later aliquoted into smaller containers, filled nearly to the top to minimize oxidation, and frozen at − 80 °C until analysis. Before storage, butylated hydroxytoluene is added to a final concentration of 75 μg/mL to prevent lipid oxidation. Since breast-milk PUFA will be expressed as a percent of total fatty acids, complete breast expressions are not required. The samples will be analysed by gas chromatography using standard methods [52].

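### Maternal blood DHA is defined as a change from baseline with no baseline adjustment stated; naming baseline DHA as a covariate would be a free gain in precision

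*Protocol article*

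**What the plan says.** Under Tertiary outcomes, the protocol article gives the maternal biomarker outcome as the difference in maternal blood DHA "from baseline to delivery and 6 months post-partum in the two treatment groups". The abstract (Methods) describes the aim of the biochemical work in the same terms: "to estimate changes in DHA levels in response to supplementation".

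A pre-treatment value will exist. The Data collection section states: "Non fasting maternal blood samples (5 ml) were obtained by veni-puncture at recruitment, delivery and 6 months postpartum". Table 1 marks maternal blood fatty acids at the same three times.

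The Statistical analyses section sets out methods for the DASII score, developmental delay, birth outcomes and growth. It names no test or model for maternal DHA. The covariates it lists for other outcomes include maternal, household, infant and dietary factors, but not baseline DHA.

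**The concern.** A plain comparison of change scores subtracts the whole baseline value, which fixes the slope of follow-up on baseline at 1. Here baseline is drawn at 20 weeks of gestation or earlier. Follow-up is months later, at delivery and again six months postpartum, with half the women supplemented in between. A slope below 1 is plausible, though the documents give no figure for it.

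If the slope is below 1, two things follow. Noise in the baseline value is carried into the outcome and widens the interval. A chance baseline difference between the groups is also over-corrected: with slope b and baseline difference D, the change-score contrast is shifted by (b − 1) × D. Using baseline as a covariate estimates the slope from the data and avoids both.

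Maternal blood is the one maternal marker measured both before and during supplementation. It helps to show that capsules recorded as taken did raise DHA status, which matters when reading the DASII result. What is at stake is how precisely that rise is estimated.

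**Working it through.** **The plan's own figures.** None is given for maternal blood DHA. The two power statements concern other outcomes:
- DASII, from Effect size, power and sample size: 0.25 SD, two-sided α = 0.05, 90% power, 338 per group. Check: n = 2 × (1.960 + 1.282)² / 0.25² = 336.2, so 337 per group by the normal formula (337.2, so 338, with the t distribution). Power at 338 is 90.1%. The figure reproduces.
- Breast-milk DHA: "150 mother-infant pairs per group, which will have 95% power to detect effect sizes of 0.5 S.D. in DHA levels". Check at two-sided 0.05: 0.5 × √(150/2) − 1.960 = 2.370, which is 99.1% power. The stated 95% is on the cautious side. Breast milk has no pre-treatment value, so the present point does not apply to it.

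**Inputs for the comparison.** From the protocol: a baseline sample, two follow-up times and 1:1 randomisation. Assumed, because the documents do not give them: the correlation r between baseline and follow-up DHA, and the ratio k of follow-up SD to baseline SD.

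**Equal SDs (k = 1).** In units of the SD²:
- variance of change = 2(1 − r)
- variance after baseline adjustment = 1 − r²
- ratio, adjusted to change = (1 + r)/2

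| r | Change | Adjusted | Adjusted/change | Interval-width ratio | Narrower by |
|---|---|---|---|---|---|
| 0.3 | 1.40 | 0.91 | 0.65 | √0.65 = 0.81 | 19% |
| 0.5 | 1.00 | 0.75 | 0.75 | √0.75 = 0.87 | 13% |
| 0.6 | 0.80 | 0.64 | 0.80 | √0.80 = 0.89 | 11% |
| 0.7 | 0.60 | 0.51 | 0.85 | √0.85 = 0.92 | 8% |

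The follow-up value alone has variance 1. Since 2(1 − r) exceeds 1 when r is below 0.5, the change score is then less precise than ignoring baseline altogether.

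**Larger follow-up SD (k = 1.5).** Ratio, change to adjusted = (k² + 1 − 2rk) / (k²(1 − r²)):
- r = 0.3: 2.35 / 2.0475 = 1.15, so adjusted intervals are about 7% narrower
- r = 0.5: 1.75 / 1.6875 = 1.04, about 2% narrower
- r = 0.7: 1.15 / 1.1475 = 1.00, no material gain

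The two approaches tie when the slope r × k equals 1, for example r = 0.5 with k = 2.

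**Effect on power.** Borrowing 338 per group for illustration, with equal SDs:
- effect of 0.25 SD: 78% (change) against 93% (adjusted) at r = 0.3; 90% against 96% at r = 0.5
- effect of 0.5 SD: above 99.9% with either method for r of 0.3 or more

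**Equivalence of the adjusted models.** Regressing change on treatment and baseline gives the same treatment estimate and standard error as regressing the follow-up value on treatment and baseline. Precision therefore depends on whether baseline is in the model, not on whether the outcome is expressed as a change.

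**The case against.** The strongest reply is that the article defines an outcome here, not an analysis. No model is stated for maternal DHA, a tertiary biomarker's model is commonly left to the SAP, and an outcome expressed as a change is compatible with baseline adjustment. For its other continuous outcomes the article regularly pairs a simple comparison with an adjusted one. All of this stands. A reader might infer that the trial plans an unadjusted change-score test in place of adjustment; the text does not say so.

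A reader might also infer that the only objective evidence of a rise in DHA is at risk. That is not supported either: the same section lists cord-blood and breast-milk DHA, and neither depends on a baseline value.

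The size is also open to challenge. r and the SDs are assumed, and supplementation or uneven adherence could widen the follow-up spread and shrink the gain. Detection of a 0.5 SD effect, the DHA effect size the protocol names for breast milk, is not in doubt.

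What remains is narrower. The change metric is the only thing the article fixes for this outcome, baseline DHA is in no listed covariate set, and the analysis closest to the wording is in large samples never more precise than the adjusted one.

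**Conclusion.** The point holds as a minor, free improvement. The tertiary maternal outcome is defined as a change with no baseline adjustment stated. Analysed as worded, it would be less precise than a comparison with baseline DHA as a covariate unless the slope of follow-up on baseline happens to be 1. With equal SDs and an assumed r of 0.3 to 0.6, adjustment narrows the interval by about 19% to 11%. With a follow-up SD 1.5 times the baseline SD, the gain falls to about 7% at r = 0.3 and 2% at r = 0.5.

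The gain is in interval width and in protection against chance baseline imbalance, not in whether a moderate DHA effect is detected. The primary DASII comparison is unaffected.

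**What to change.** Add one sentence to the Statistical analyses section, or to the SAP if it is not already there: maternal DHA at delivery and at 6 months postpartum (or its change from baseline) will be compared between the DHA and placebo groups in a linear model with treatment and baseline DHA, or in one repeated-measures model with baseline DHA as a covariate. Report mean change by group as a descriptive summary. The sentence would also make explicit that the contrast is between groups, which the outcome wording leaves to be inferred.

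The cost is that sentence. The baseline sample is already in the schedule, no further data are needed, and nothing changes for participants.

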### Ethical approvals

Ethical clearances were obtained from all participating institutions including: Chronic Disease Control (CCDC-IEC_04_2015), Public Health Foundation of India (TRC-IEC-261/15), Jawaharlal Nehru Medical College (MDC/IECHSR/2016–17/A-85) and All India Institute of Medical Sciences (IEC-28/17.11.2015). The trial is registered retrospectively at the clinicaltrials.gov (NCT01580345, NCT03072277) and ctri.nic.in (CTRI/2013/04/003540, CTRI/2017/08/009296). Trial registration was completed after participant recruited had started. An independent Data and Safety Monitoring Board (DSMB) was constituted before the start of the trial to review the study data periodically to monitor safety and outcomes.

### Effect size, power and sample size

The primary outcome variables are infant motor and mental development quotient at 12 months of age. The smallest effect sizes of interest were 0.25 S.D. for motor and mental development at 12 months of age [42]. Using a two-tailed test and a significance level of α = 0.05, a final sample of 338 infants per group (676 mother-child dyads) was required at the end of the study (12 months postpartum) to provide 90% power. A total of 957 mothers have been recruited in the present study, allowing for potential attrition due to serious adverse events, withdrawal, and migration out of the study area. Breast-milk samples are being collected within 3–4 days after delivery and at 1 month and 6 months postpartum from a 30% convenience sub-sample - 150 mother-infant pairs per group, which will have 95% power to detect effect sizes of 0.5 S.D. in DHA levels.

### Recruitment

The pregnant women were screened by the project officer with the help of the attending medical doctor to verify eligibility. A project officer then explained the study in detail and invited the eligible candidate for participation. Written informed consent was provided by all willing participants in presence of a family member. The copy of the informed consent and subject information sheet were provided in their preferred local language (Kannada, Marathi or Hindi).

### Randomization procedure

Consenting women were randomized to their treatment group by the project officer. The randomization scheme consisted of a sequence of blocks such that each block contained a pre-specified number of treatment assignments in random order. The block size of 2, 4 and 6 was used for treatment allocation. The randomization code list was pre-generated for 1200 women randomly allocating 600 participants to the DHA and 600 participants to placebo group. The assignment codes were placed in sealed envelopes at the beginning of the study, and these envelopes were kept sealed at the host institution by a staff-member not involved in the trial.

### Data collection

Primary outcome variable: The development quotient (DQ) among infants at 12 months of age assessed using the standardized DASII scale [43, 44] by two trained psychologists is the primary outcome variable [45, 46]. DASII is the Indian modification (done in 1970 and 1977) of the Bayley Scale of Infant Development (BSID) using Indian norms for 67 motor and 163 mental items of the BSID. DASII provides a measure of DQ among Indian infants below 30 months of age [47, 48]. DQ is defined as the ratio of functional to chronological age. Third, 50th and 97th percentile norms are given. The maximum DQ score is 100; ≥85 is normal; 71–84 is mild to moderate delay and developmental delay is defined as DQ ≤70 (≤2SD). Median reliability index for motor and mental scales based on correlation between consecutive months is noted to be 0.88 for motor scales and 0.91 for mental scales. The motor development items cover the child’s development from supine to erect posture, neck-control, locomotion etc. It also includes the record for manipulative behaviour such as reaching, picking-up, handling things etc. The mental development items record the child’s cognizance of objects in the surroundings, perceptual pursuit of moving objects, exploring them to meaningful manipulation. It also covers the development of communication and language comprehension, spatial relationship and manual dexterity, imitative behavior and social interaction etc. Each child undergoes DASII assessment twice – once at 6 months and again at 12 months. For infants born preterm, the assessment is done at their corrected ages of 6 and 12 months.
Secondary outcomes:Birth outcomes – Data are collected by a research assistant from hospital records within 24 h after delivery. In case of night deliveries, records from hospital staff are obtained the next morning. All hospital staff were apprised of the variables being collected, procedures and data collection methods before the start of the trial. A periodic (every 6 months) refresher training has also been provided to the staff. The data include whether the birth was a live birth, sex of baby, type of delivery, and anthropometric measurements. Birth weight is measured to the nearest 10 g by using a digital pediatric scale. Low birth weight is defined as recorded birth weight less than 2500 g. Birth length and head circumference are measured by trained hospital staff to the nearest 1 mm using a portable anthropometer with a fixed headpiece and a flexible tape, respectively, according to standard procedures. Gestational age at birth in days is determined based on the dating ultrasound. Preterm delivery is defined as delivery after 20 weeks and before 37 weeks of completed gestation. Foetal losses during pregnancy – including miscarriages/abortions and still-births are recorded by study personnel on site or details are brought by field workers (in case mother went to any other hospital). Stillbirths are defined as fetuses delivered at 20 weeks of gestation or later with no signs of life and recorded as occurring before or during the onset of labor; neonatal deaths are defined as deaths among live-born infants occurring within 28 days after delivery.Infant weight, length and head circumference at 6 and 12 months are measured during their scheduled PKH visits. Questions about infant’s health are asked by the field-staff during home-visits (postpartum). Copies of the health-reports from the child’s paediatrician (whether at PKH or elsewhere) are collected. After the screening procedure, at the time of recruitment, data for contact information, maternal obstetric medical history, demographic details and socio-economic status also have been collected by the trained research assistant using pre-tested questionnaires. Anthropometric measurements of both mother and father have been recorded. Dietary intakes of fatty acids were evaluated using a previously validated food-frequency questionnaire adapted for use in pregnant women (recall period- past 3 months) also have been recorded.Fatty acid profile: Fatty acid composition of RBC membrane phospholipids are appropriate biomarkers of fatty acid status and reflects dietary intakes. Linoleic acid (18:2n-6); Alpha-linolenic acid (18:3n-3); Arachidonic acid (20:4n-6); Eicosapentanoic Acid (20:5n-3); DHA (22:6n-3) will be measured for this study. Lipids will be extracted form the RBC membrane, phospholipid fraction will be separated by thin layer chromatography (TLC), esterified by procedure described by Lepage and Roy [49] and subjected to gas chromatography (GC) for separation and identification. Non fasting maternal blood samples (5 ml) were obtained by veni-puncture at recruitment, delivery and 6 months postpartum. Neonatal blood samples were obtained from the umbilical cord vein immediately after delivery using the syringe method [50]. A 2 ml venous blood sample was obtained 12 months of age from infants. All samples were collected into tubes containing disodium ethylene diamine tetraacetic acid (EDTA). Plasma and RBCs were separated by cold centrifugation at 800 g for 10 min. Plasma was aliquoted and stored at − 80 °C for later analysis.Breast-milk polyunsaturated fatty acids (PUFAs): Breast-milk samples (1 day, 1 month and 6 months postpartum) are taken from 30% random sub-sample. The milk-samples are from a morning feed but not the first one, between 8 and 12 o’clock at PKH. Infants are allowed to suckle the nipple for a few minutes, and then a breast-milk sample (10 ml) is expressed (manual, by mothers themselves) and the feeding continued [51]. The samples are refrigerated immediately (to prevent bacterial growth) and later aliquoted into smaller containers, filled nearly to the top to minimize oxidation, and frozen at − 80 °C until analysis. Before storage, butylated hydroxytoluene is added to a final concentration of 75 μg/mL to prevent lipid oxidation. Since breast-milk PUFA will be expressed as a percent of total fatty acids, complete breast expressions are not required. The samples will be analysed by gas chromatography using standard methods [52].

### Training of staff and calibration of equipment

The personnel for DHANI trial were recruited from local areas and trained before the start of the trial and refresher training was provided every 6 months thereafter. The training imparted an understanding of the trial objectives, study procedures, data collection methods, supplement distribution; recording in the requisite case record forms (CRFs), etc. The personnel used local language for communication with the participants and their families on site (Kannada, Marathi, Hindi).

Standardization (calibration) of measuring instruments is done every 4 months by checking the measuring instruments against an accurate standard to determine any deviation and to correct errors.

